- [12] Echocardiogram: one examination within 7 days prior to randomization, 7 days prior to surgical resection and at the end-of-treatment visit, plus additional examinations for clinically significant electrocardiographic abnormalities during the study period.
- [13] Pregnancy test: For women of childbearing potential, a serum pregnancy test is used. Performed within 7 days prior to first dose, 1 week prior to surgery, 3-6 weeks after surgery, end of treatment/withdrawal from study, and at Visit 1 of the safety follow-up period.
- [14] Imaging: including chest CT, abdominal ultrasound; PET-CT testing and cranial magnetic resonance MRI (1.5T scanning + enhancement; cranial CT may be used instead if the patient has a contraindication to magnetic resonance testing) may be performed up to 60 days prior to the first use of the study medication; bone scans will be performed only when clinically indicated, and the bone scans must have been performed within 42 days prior to the first dose of medication.
- ✓ Screening cycle, tumor assessment can be up to 4 weeks prior to first use of study drug, and imaging results obtained prior to signing informed consent can be used for screening period tumor assessment as long as they meet RECIST 1.1 requirements.
  - ✓ Full imaging evaluation was performed after the 2nd cycle of dosing and within 7 days prior to surgery for lung cancer.
  - ✓ Subjects in whom no imaging progression is observed during safety follow-up and survival follow-up should continue to have imaging evaluations at the same frequency until disease progression or initiation of other antitumor therapy.
  - ✓ In addition to disease progression confirmed by imaging, subjects who end treatment for other reasons should also be imaged as often as possible at the frequency specified in the protocol until documented confirmation of disease progression, initiation of new antitumor therapy, or death.
- [15] Lung function assessment: Normal or mild to moderate abnormal lung function ( $VC\% > 60\%$ ,  $FEV1 > 1.2L$ ,  $FEV1\% > 40\%$ ,  $DLco > 40\%$ ) to tolerate radical lung cancer surgery; assessed within 14 days prior to the first dose of drug, and once within 7 days prior to lung cancer resection.
- [16] Pathologic evaluation: pathologic diagnosis and evaluation within 90 days prior to first dose and after lung cancer resection, respectively.

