#### **3.3 Secondary endpoints**

Observe the postoperative major pathologic response (MPR) rate, event-free survival (EFS) and overall survival (OS).

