\*1 cycle = 3 weeks, treatment duration = 3 cycles

The medication record (Sintilimab and anlotinib) is confirmed through the following table.

A Prospective Single-arm, Open-label Study of Sintilimab and Anlotinib Combined with Chemotherapy in Neoadjuvant Treatment of Resectable NSCLC

Research Center Name/No.: The Second Affiliated Hospital of Air Force Medical University (Tangdu Hospital)/01  
Principal Investigator: [name]

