#### **4.4 Radical surgery**

Within 4-6 weeks (22-42 days) of the last dose, the radical surgery was performed.

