### 5.1.2 Other indicators

- Major pathologic response (MPR) rate, defined as the proportion of subjects with  $\leq 10\%$  surviving tumor cells in the resected primary tumor and all resected lymph nodes. For pathological assessments, primary lung tumors and lymph node specimens were staged using the AJCC criteria (8th edition). Residual viable tumor percentage in primary tumors was determined from routine hematoxylin and eosin-stained specimens. Tumors with  $\leq 10\%$  viable cells were classified as having MPR. Pathological downstaging was defined as a reduction in ypTNM stage post-treatment, with no new lesions or progression of existing lesions.

- Event-free survival (EFS), defined as the interval from enrolment to the

earliest occurrence of local progression resulting in inoperability; unresectable tumour, disease progression or recurrence according to RECIST version 1.1 as assessed by the investigator; or death from any cause. Progression-free survival was treated as censored on the date of the last validated tumor assessment for subjects in whom no tumor progression or death was observed.

- Overall survival (OS), defined as the time from study entry (i.e., after signing ICF) to death from any cause. Subjects who were alive at the time of last contact had their overall survival censored at the date of last contact.

- Patients underwent radiological evaluations by investigators according to RECIST version 1.1 at baseline, after two cycles of neoadjuvant therapy, prior to surgical resection, and every 4 cycles during adjuvant therapy until disease progression, intolerable toxicity, death, or withdrawal of consent. Complete and partial responses were confirmed radiologically at least 4 weeks later, while stable disease was confirmed at least 8 weeks after the initial assessment. The ORR was defined as the proportion of patients achieving either a complete or partial response. Patients were followed up by visits or phone calls every 12 weeks to determine survival status.

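### The 4-week confirmation rule for CR/PR in section 5.1.2 cannot be met by a response first seen at the pre-operative scan, so ORR is biased downward if it counts only confirmed responses

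*Protocol*

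**What the plan says.** Section 5.1.2 places investigator RECIST 1.1 assessments "at baseline, after two cycles of neoadjuvant therapy, prior to surgical resection, and every 4 cycles during adjuvant therapy". Note [14] to the Study Flow Chart fixes the two pre-surgical time points: "Full imaging evaluation was performed after the 2nd cycle of dosing and within 7 days prior to surgery for lung cancer".

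The same bullet of 5.1.2 then sets the confirmation rules. For response, "Complete and partial responses were confirmed radiologically at least 4 weeks later"; for stable disease, "stable disease was confirmed at least 8 weeks after the initial assessment". The next sentence reads "The ORR was defined as the proportion of patients achieving either a complete or partial response". It does not contain the word 'confirmed'.

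The dates follow from section 3.6.1 ("1 cycle = 3 weeks, treatment duration = 3 cycles") and section 4.4 ("Within 4-6 weeks (22-42 days) of the last dose, the radical surgery was performed"). Neither section says whether the last dose is the cycle-3 infusion or the last anlotinib capsule.

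ORR appears only in 5.1.2. The primary endpoints in section 3.2 are pCR and safety. The secondary endpoints in section 3.3 are MPR, EFS and OS.

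**The concern.** A confirmation rule needs a later scan of the same lesion. Here the lesion is removed within days of the second on-treatment scan, and scans in the adjuvant or follow-up phase cannot confirm shrinkage of a tumor that is no longer there. If the rule is applied, patients whose tumors first reach CR or PR after the third cycle drop out of the numerator because of the schedule and not because the response failed to last. Some patients who responded after cycle 2 could drop out too, depending on their operating date.

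If the rule is not applied, the text is still a problem. Whether ORR is confirmed or unconfirmed could be settled after the results are seen, in an open-label, single-arm trial with investigator-read imaging. Section 1.1.3 quotes an ORR of 78.5% from an earlier trial of nivolumab plus chemotherapy, so readers are likely to set this trial's ORR beside it.

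**Working it through.** The protocol gives no expected ORR, so there is no figure of its own to reproduce. The check is calendar arithmetic.

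**Inputs**
- Three 21-day cycles (3.6.1): cycle 1 starts on day 1, cycle 2 on day 22, cycle 3 on day 43.
- Anlotinib on days 1-14 of each cycle (3.6.1): last cycle-3 dose on day 43 + 13 = 56.
- Surgery 22-42 days after the last dose (4.4).
- Pre-operative scan 0-7 days before surgery (flow chart note [14]).
- Post-cycle-2 scan at the end of cycle 2, taken as day 43. Day 42 adds one day to every gap below.
- Confirmation interval: 4 × 7 = 28 days.

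**Response first seen at the pre-operative scan**

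Time left before resection is 0-7 days, which is less than 28. It is never confirmable in a resected patient.

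**Response first seen after cycle 2**

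Gap = (last dose + 22 to 42) − (0 to 7) − 43.

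| Last dose | Surgery (day) | Pre-operative scan (day) | Gap (days) |
|---|---|---|---|
| Infusion, day 43 | 65-85 | 58-85 | 15-42 |
| Anlotinib, day 56 | 78-98 | 71-98 | 28-55 |

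With the first scan on day 42 the gaps are 16-43 and 29-56.

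Under the infusion reading, on an even grid of 21 surgery days and scan leads of 1-7 days, 77 of 147 combinations (52%) reach 28 days. Under the anlotinib reading all 147 do. The even grid is an assumption; the protocol gives no distribution of operating dates.

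Two features of the protocol move these numbers:
- The window is written both as 4-6 weeks and as 22-42 days, yet 4 weeks is 28 days. With a 28-day lower limit the gaps become 21-42 and 34-55 days, and the infusion grid gives 77 of 105 (73%). The two statements of the window need reconciling.
- The flow chart allows ±7 days unless otherwise noted. A first scan on day 50 would lower the minimum gap to 58 − 50 = 8 days (infusion) or 71 − 50 = 21 days (anlotinib).

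**Stable disease (8 weeks = 56 days)**

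If the initial assessment is baseline, the earliest pre-operative scan (day 58) is already 57 days after day 1, so the rule is met. If it is the post-cycle-2 scan, the longest gap is 42-43 or 55-56 days, so the rule is essentially out of reach before surgery. The text does not say which is meant.

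**Illustration of size (assumed values)**

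Let U be the unconfirmed ORR and f the share of responders first seen at the pre-operative scan. If all are resected, confirmed ORR ≤ U × (1 − f).

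| U | f = 10% | f = 20% | f = 30% | f = 40% |
|---|---|---|---|---|
| 50% | 45% | 40% | 35% | 30% |
| 60% | 54% | 48% | 42% | 36% |
| 70% | 63% | 56% | 49% | 42% |

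For U = 60% and 45 patients, the loss is 45 × 0.60 × f: 2.7 patients at f = 10% and 10.8 at f = 40%, about 3 to 11. These are upper limits for the confirmed ORR, because some post-cycle-2 responses may also go unconfirmed.

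**The case against.** The strongest reply is that the protocol never says ORR counts confirmed responses only. The defining sentence speaks simply of CR or PR, and the Tumor Assessment Form has an overall-response entry with no visible confirmation field. This stands in part: the downward bias is conditional on a reading. But the ORR sentence directly follows the confirmation rule, so confirmed ORR is the natural reading, and the other reading needs the same sentence edited.

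A reader might infer that no response seen before surgery can ever count. The schedule does not support that. The pre-operative scan can confirm a post-cycle-2 response whenever the gap reaches 28 days: part of the window if the last dose is the infusion, all of it on schedule if it is anlotinib. Anlotinib is a study drug, so the second reading is reasonable. A patient who is not resected may also still be confirmed later.

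A reader might also infer that stable disease can hardly ever be confirmed. That fails if the initial assessment means baseline, and stable disease does not enter ORR in any case.

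Section 3.6.1 mentions evaluation after three cycles, which could suggest a further scan. Section 5.1.2, flow chart note [14] and the Tumor Assessment Form name no such separate scan; the pre-operative assessment is the likely meaning.

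Finally, ORR is not a listed endpoint, and no hypothesis, stopping rule or sample size uses it. That is correct and limits the weight of the point.

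**Conclusion.** The point holds in a limited form. Section 5.1.2 states a confirmation rule that the protocol's own schedule cannot satisfy for one group: resected patients whose CR or PR is first seen at the pre-operative scan. For responses first seen after cycle 2, whether the rule can be met depends on an undefined term (last dose) and on the operating date.

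If the rule is enforced for ORR, the direction of the bias is certain, since confirmation can only remove responders. Its size is not computable from the protocol; the fall from 60% to between 54% and 36% rests wholly on assumed values. It would go too far to say that ORR is certainly understated, because the definition does not explicitly require confirmation.

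The consequence is confined to a descriptive indicator. The pCR analysis and its two-stage rule are untouched. The text is nevertheless wrong as written and worth correcting.

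**What to change.** In section 5.1.2, define ORR as the proportion of patients whose best RECIST 1.1 response up to the last scan before surgery is CR or PR, and label it unconfirmed. Remove the 4-week confirmation requirement for ORR. For patients who are never operated on, name the equivalent last scan. In the 8-week stable-disease rule, state whether the initial assessment means baseline.

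No change of denominator is needed for this point. The cost is a sentence-level edit, with no added scans or patients. The one drawback is that the resulting ORR must be reported as unconfirmed and should not be set beside confirmed rates without saying so.

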**Tumor Assessment Form (RECIST 1.1 )**

|                                                                                                                                                                                                                                                          |                             |               |                       |                                              |              |                                                                                                                                        |                 |                                                                                                                    |                                                                                                                                        |
|----------------------------------------------------------------------------------------------------------------------------------------------------------------------------------------------------------------------------------------------------------|-----------------------------|---------------|-----------------------|----------------------------------------------|--------------|----------------------------------------------------------------------------------------------------------------------------------------|-----------------|--------------------------------------------------------------------------------------------------------------------|----------------------------------------------------------------------------------------------------------------------------------------|
| Center No.:                                                                                                                                                                                                                                              |                             | Center Name:  |                       | Screening period                             |              | Subject initials:                                                                                                                      |                 | Subject No.:                                                                                                       |                                                                                                                                        |
| Principal Investigator:                                                                                                                                                                                                                                  |                             |               |                       | Upon completion of two cycles of neoadjuvant |              |                                                                                                                                        |                 | Preoperative evaluation (week from C1D1)                                                                           |                                                                                                                                        |
| Examination methods 1. plain CT 2. enhanced CT or plain + enhanced CT 3. plain MRI 4. enhanced MRI or plain + enhanced MRI 5. bone scan 6. PET 7. PET-CT 8. ultrasound 99. others, please specify                                                        |                             |               |                       |                                              |              |                                                                                                                                        |                 |                                                                                                                    |                                                                                                                                        |
| Target lesion                                                                                                                                                                                                                                     |                             |               |                       |                                              |              |                                                                                                                                        |                 |                                                                                                                    |                                                                                                                                        |
| Lesion No.                                                                                                                                                                                                                                               | Lesion location             |               | Inspection Method No. | Inspection date                              | Is the layer | Longest diameter (non-lymph node lesions) or                                                                                           | Inspection date | Is the layer                                                                                                       | Longest diameter (non-lymph node lesions) or                                                                                           |
| 01                                                                                                                                                                                                                                                       | Anatomical site (left lung) | Specific part |                       |                                              |              | mm                                                                                                                                     |                 |                                                                                                                    | mm                                                                                                                                     |
| 02                                                                                                                                                                                                                                                       |                             |               |                       |                                              |              | mm                                                                                                                                     |                 |                                                                                                                    | mm                                                                                                                                     |
| 03                                                                                                                                                                                                                                                       |                             |               |                       |                                              |              | mm                                                                                                                                     |                 |                                                                                                                    | mm                                                                                                                                     |
| 04                                                                                                                                                                                                                                                       |                             |               |                       |                                              |              | mm                                                                                                                                     |                 |                                                                                                                    | mm                                                                                                                                     |
| 05                                                                                                                                                                                                                                                       |                             |               |                       |                                              |              | mm                                                                                                                                     |                 |                                                                                                                    | mm                                                                                                                                     |
| Sum of the longest/shortest diameters of all target lesions                                                                                                                                                                                              |                             |               |                       |                                              |              | mm                                                                                                                                     | mm              |                                                                                                                    |                                                                                                                                        |
| Assessment of target lesion efficacy: comparison with baseline or minimum                                                                                                                                                                                |                             |               |                       |                                              |              | NA                                                                                                                                     |                 | %                                                                                                                  |                                                                                                                                        |
| Non-target lesion status:                                                                                                                                                                                                                                |                             |               |                       |                                              |              | FYes FNo                                                                                                                               |                 | %                                                                                                                  |                                                                                                                                        |
| Lesion No.                                                                                                                                                                                                                                               | Lesion location             |               | Inspection Method No. | Inspection date                              | Is the layer | Non-target lesion status                                                                                                               | Inspection date | Is the layer                                                                                                       | Non-target lesion status                                                                                                               |
| Non-target lesion status: Please check options:  A present  B absent  C significantly progressed  D unable to assess  E not done |                             |               |                       |                                              |              |                                                                                                                                        |                 |                                                                                                                    |                                                                                                                                        |
| 01                                                                                                                                                                                                                                                       |                             |               |                       |                                              |              |  A  B  C  D  E |                 |                                                                                                                    |  A  B  C  D  E |
| 02                                                                                                                                                                                                                                                       |                             |               |                       |                                              |              |  A  B  C  D  E |                 |                                                                                                                    |  A  B  C  D  E |
| 03                                                                                                                                                                                                                                                       |                             |               |                       |                                              |              |  A  B  C  D  E |                 |                                                                                                                    |  A  B  C  D  E |
| 04                                                                                                                                                                                                                                                       |                             |               |                       |                                              |              |  A  B  C  D  E |                 |                                                                                                                    |  A  B  C  D  E |
| 05                                                                                                                                                                                                                                                       |                             |               |                       |                                              |              |  A  B  C  D  E |                 |                                                                                                                    |  A  B  C  D  E |
| Non-target lesion efficacy evaluation: CR Non-CR/Non-PD NE NA                                                                                                                                                                                            |                             |               |                       |                                              |              | NA                                                                                                                                     |                 | CR  Non-CR/Non-PD  PD                                              |                                                                                                                                        |
| Any new lesions since last imaging test                                                                                                                                                                                                                  |                             |               |                       |                                              |              | NA                                                                                                                                     |                 | CR  Non-CR/Non-PD  PD                                              |                                                                                                                                        |
| Lesion No.                                                                                                                                                                                                                                               | Lesion location             |               | Inspection Method No. | Inspection date                              | Is the layer | Type of pathology (if done)                                                                                                            | Inspection date | Is the layer                                                                                                       | Type of pathology (if done)                                                                                                            |
| Any splitting or fusion of lesions since last imaging test                                                                                                                                                                                               |                             |               |                       |                                              |              |                                                                                                                                        |                 |                                                                                                                    |                                                                                                                                        |
| Description of lesion splitting or fusion (please record the status of splitting or fusion)                                                                                                                                                              |                             |               |                       |                                              |              | NA                                                                                                                                     |                 | Description:                                                                                                       |                                                                                                                                        |
| Overall efficacy assessment: CR; PR; SD; PD; NE                                                                                                                                                                                                          |                             |               |                       |                                              |              | NA                                                                                                                                     |                 | CR  PR  SD  PD  NE |                                                                                                                                        |
| Signature of investigator/authorized imaging physician and date                                                                                                                                                                                          |                             |               |                       |                                              |              |                                                                                                                                        |                 |                                                                                                                    |                                                                                                                                        |

